### Treatment implementation

ADT will be initiated 3 months before WPRT (Fig. 1). In the intermediate-risk group, ADT will be administered for 6 months, whereas in high-risk group, long-term ADT for 2–3 years will be administered. Administration of antiandrogens and/or luteinizing hormone-releasing hormone agonists is allowed for patients in this study.

Before computed tomography (CT) for treatment planning, an experienced radiologist will insert three gold intra-prostatic fiducial markers via endorectal sonography for CyberKnife tracking. One week later, enhanced CT scans with a slice thickness of 2.5 mm will be obtained in all patients who will have empty bladders and rectal balloons in place. Participants should be in a relaxed supine position facilitated by an ankle pillow. Afterwards, a radiation oncologist will delineate organs-at-risk (OAR) and target volumes. If available, fusion with diagnostic magnetic resonance imaging (MRI) is recommended. Gross target volume (GTV) includes whole prostate glands, involved extraprostatic tissues, and any suspicion of involvement of the seminal vesicles. If seminal vesicle invasion is excluded definitely, they will not be included in the GTV calculation. Clinical target volume (CTV) includes regional nodal areas including obturator, external/internal iliac, and presacral lymphatic areas. Planning target volume (PTV) is expansion of CTV margins by 5 mm, except for the posterior 3-mm margin for rectal sparing. PTV must be irradiated with ≥ 95% of the prescription dose. OAR includes the rectum, bladder, and femoral heads, and all are contoured according to the Radiation Therapy Oncology Group guidelines [18]. IMRT will be used, and the dose regimen will be 44 Gy in 2.2-Gy fractions every weekday. Dose constraints are as follows: (1) bowel (small and large), 30% of the entire bowel volume must not receive more than 40 Gy; (2) rectum, 60% of the volume must receive ≤ 40 Gy; (3) bladder, 35% of the bladder volume must receive ≤ 45 Gy; (4) femoral heads, 15% of the femoral head volume must receive < 35 Gy. WPRT will be initiated within 10 days after the day of CT for treatment planning. For image guidance, daily cone-beam CT will be used. Patients will be asked to empty their bladder before each fraction, while there will be no routine bowel preparation.

For SBRT boost planning, another non-enhanced CT with 1.25-mm slices will be obtained at 1 week before the start of the boost therapy. Patients will be in a supine position with a vacuum cushion and an ankle pillow and with an empty bladder and a Foley catheter inserted for delineation of the urethra. The rectal balloon will not be used for the boost therapy. Boost volume is identical to the GTV of WPRT delineation, whereas the PTV margin is 3 mm in all directions. The urethra as well as the rectum and bladder are also included in the OAR. The CyberKnife robotic radiosurgery system (Accuray Incorporated, Sunnyvale, CA, USA) will be utilized for the SBRT boost, and the PTV must receive ≥ 80% and < 120% of the prescribed dose. OAR dose constraints are as follows: (1) rectum, < 85% of prescription dose; (2) bladder and urethra, < 100% of prescription dose. Prescription doses are 18 Gy and 21 Gy in three fractions, every other day. Tracking for fiducial markers will be used for image-guided radiotherapy. An enema will be performed for bowel preparation before every treatment. The whole radiotherapy period will not exceed 10 weeks.

### Data collection and follow-up period

Patient data will be collected before start of radiotherapy, every week during WPRT, at the end of WPRT, at the end of SBRT boost, and at 1-month and 4-month follow-up visits after radiotherapy (Fig. 2). Patient data will be documented in Case Report Forms on urologic/gastrointestinal toxicities using the Common Toxicity Criteria for Adverse Events (CTCAE v 4.03), patient-reported outcomes (PRO), and PSA levels. After confirmation of the CyberKnife boost plan (at fourth week of radiotherapy), the evaluation of toxicities and efficacy will be no longer be blind. For ADT initiation, patients will be evaluated by the Department of Urology during follow-up visits every 3 months. After radiotherapy sessions, patients will also be evaluated by the Department of Radiation Oncology every 3 months for the first 2 years, every 6 months until 5 years, and annually thereafter. Follow-up evaluations will assess chronic toxicities and PSA levels. If clinical recurrence is suspicious, imaging studies, such as MRI and/or bone scans, will be considered.

**Fig. 2 Fig2:**
[figure not shown]
Intervention and assessment schedule for the trial according to the Recommendations for Interventional Trials (SPIRIT)

For the patient data protection, separate identification code will be given to all patients. Also, data will be protected by password-accessible files, and only investigators can assess the files. All data will be deleted at 3 years after the end of the study.

### Assessment of primary and secondary endpoints

Primary endpoints of this trial are acute toxicities and short-term biochemical control. Acute toxicities are defined as events occurring within 3 months after treatment and are evaluated according to the CTCAE v 4.03 and PRO, using the Overactive Bladder Symptom Score and the International Prostate Symptom Score. Secondary endpoints are chronic toxicities and long-term biochemical control. Chronic toxicities are evaluated using the Late Effects of Normal Tissues scoring system. Biochemical recurrence (BCR) is defined as the Phoenix consensus definition of a rise in PSA level by 2 ng/ml or more above the nadir value [19].

The trial design and protocol adhere to the Recommendations for Interventional Trials (SPIRIT) criteria. The SPIRIT Checklist and Figure can be found in Additional file 1: Table S1 and Fig. 2.

### Statistical analysis

The present study is being performed as a purely exploratory pilot study; therefore, by calculation for statistical analysis, a total 15 patients in each treatment group is considered as an appropriate sample size. Comparison of the treatment two groups will be conducted using the chi-square test or Fisher’s exact test. Biochemical recurrence-free survival (BCRFS) will be calculated from the ADT start date using the Kaplan-Meier method. Descriptive statistics of all analyzed parameters will be provided, whenever appropriate.

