## Methods/design

### Recruitment and study design

This prospective, randomized, single-center, pilot study on intermediate- and high-risk prostate cancer patients is ongoing at Asan Medical Center. Patients are randomized into two groups with a 1:1 allocation using blocked randomization, and the random block size is 4. The randomization sequence is generated by the clinical research nurse using Excel software. The allocation sequence is concealed from the primary investigator who enrolls the patients using the Excel file locked with a password. Also, the file is saved in a computer located in the place that the primary investigator cannot approach. One group will receive a CyberKnife SBRT boost dose of 18 Gy administered in three fractions (18-Gy group), and the other group will receive a CyberKnife SBRT boost dose of 21 Gy administered in three fractions (21-Gy group).

As shown in Fig. 1, all patients will first receive ADT. Several studies strongly support the use of ADT in addition to EBRT, long-term (i.e., 2–3 years) ADT for high-risk patients [13, 14] and short-term ADT (4–6 months) for the intermediate group [15, 16]. Risk group definition is based on the current National Comprehensive Center Network guidelines (https://www.nccn.org/professionals/physician_gls/pdf/prostate.pdf). Informed consent of patients is mandatory before recruitment and is obtained from the radiation oncologists. Three months after the start of ADT, WPRT (44 Gy in 20 fractions) with intensity-modulated radiotherapy (IMRT) will be initiated. Next, CyberKnife boost will be implemented. Since the primary investigator has to confirm the plan for CyberKnife boost, the blinding is not possible afterward.

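### The only between-arm test named is a test for counts, which does not suit the two numeric symptom scores in the primary acute-toxicity endpoint

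*Protocol article*

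**What the plan says.** **Comparison method.** Under Statistical analysis, the article says: "Comparison of the treatment two groups will be conducted using the chi-square test", or Fisher's exact test. No other between-arm comparison is named. Kaplan-Meier is given for biochemical recurrence-free survival, but as an estimate without a test. The same section adds: "Descriptive statistics of all analyzed parameters will be provided, whenever appropriate".

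**Endpoint.** Under Assessment of primary and secondary endpoints: "Primary endpoints of this trial are acute toxicities and short-term biochemical control". Acute toxicity covers the 3 months after treatment and is measured by CTCAE and by "PRO, using the Overactive Bladder Symptom Score and the International Prostate Symptom Score". No cut-off or category is given for either score.

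**Visits.** The section Data collection and follow-up period sets the schedule: "Patient data will be collected before start of radiotherapy, every week during WPRT, at the end of WPRT, at the end of SBRT boost". Two later visits follow, 1 and 4 months after radiotherapy. The data listed for these visits include "patient-reported outcomes (PRO), and PSA levels".

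**Size.** Allocation is 1:1, and "a total 15 patients in each treatment group is considered as an appropriate sample size". The study is described as purely exploratory. No alpha, power, effect size or SD is stated.

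**The concern.** Chi-square and Fisher tests need categories. To apply either one to OABSS or IPSS, someone must choose a cut-point, and the article supplies none. Cutting discards the size of each patient's change. A plain two-by-two comparison at a follow-up visit also leaves chance baseline differences between two groups of 15 in the result, although a pre-radiotherapy value is available to remove them.

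This sits badly with the article's own argument. The Discussion defends patient-reported outcomes on the ground that clinicians miss or understate toxicity, and it expects a more precise assessment from them. The results are meant to inform a phase II study that selects the boost dose. What that study needs from the pilot is an estimated difference in the scores, its uncertainty and the SD, rather than a p-value from a two-by-two table.

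A cut-point fixed late would also be exposed to choice after the fact, because the article says assessment is no longer blind once the boost plan is confirmed in the fourth week of radiotherapy.

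**Working it through.** **The plan's own figure.** Fifteen per arm is said to come from a calculation, but no inputs are given, so it cannot be reproduced.

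**Inputs from the article.** n = 15 per arm, 1:1; chi-square or Fisher; two numeric scores with a pre-radiotherapy value.

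**Inputs assumed.** Two-sided 5%; normally distributed scores with equal SD; true standardised difference d = 0.5 to 1.2; baseline correlation r = 0.5 (0.3 and 0.7 as sensitivity); no dropout; cut at the midpoint between the arm means.

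**Formulas.**
- Unadjusted t-test: noncentral t, 28 df, noncentrality d × √(n/2) = d × √7.5 = 2.739 d.
- ANCOVA: noncentral t, 27 df, noncentrality 2.739 d / √(1 − r²). At r = 0.5 the divisor is 0.866. For d = 1.0 this gives 2.739 / 0.866 = 3.16.
- Cut score: the proportions above the cut are Φ(−d/2) and Φ(d/2). For d = 1.0 these are 0.31 and 0.69. Power is the exact binomial probability of a significant table, summed over all 16 × 16 outcomes. Chi-square is without continuity correction.

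**Power at 15 per arm, r = 0.5.**

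| d | ANCOVA | t-test | Chi-square, cut | Fisher, cut | Loss, chi-square vs ANCOVA | Loss, Fisher vs ANCOVA |
|---|---|---|---|---|---|---|
| 0.5 | 33% | 26% | 18% | 9% | 46% | 72% |
| 0.8 | 68% | 56% | 39% | 25% | 43% | 64% |
| 1.0 | 86% | 75% | 56% | 39% | 36% | 54% |
| 1.2 | 96% | 89% | 71% | 56% | 25% | 42% |

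Loss is 1 minus the ratio of unrounded powers; at d = 0.8 with chi-square, 1 − 0.389/0.684 = 43%.

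**Sensitivity.**
- *Baseline correlation.* At d = 1.0 the Fisher loss is 50% for r = 0.3 and 59% for r = 0.7; the chi-square loss is 30% and 42%. For chi-square at r = 0.7, the loss exceeds half only at the smaller effects (61% at d = 0.5, 54% at d = 0.8).
- *Cutting alone.* Against the unadjusted t-test, chi-square loses 26–32% and Fisher 48–65% for d = 0.5 to 1.0.
- *Fisher's conservatism.* With equal proportions of 50%, the actual size is 1.7% for Fisher and 4.6% for chi-square. Part of Fisher's loss comes from this and not from cutting.
- *Where the cut falls.* At the midpoint the expected count per cell is 15 × 0.5 = 7.5, so chi-square would ordinarily be used. With 20% above the cut in the 18-Gy arm, and Fisher used only when an expected count is below 5, power is 11%, 32% and 50% at d = 0.5, 0.8 and 1.0. The losses are 66%, 54% and 42%.
- *Keeping baseline while cutting.* Dichotomised change from baseline at r = 0.7, d = 0.8 gives 58% (chi-square) or 42% (Fisher), against 84% for ANCOVA.

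**The case against.** The strongest reply has four parts.

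**The text does not say the scores will be cut or baseline dropped.** This stands. The scores might only be described, or be categorised as change from baseline. The power figures are therefore conditional on a midpoint cut without baseline. What the text does say, without qualification, is that the groups will be compared by chi-square or Fisher, and neither fits a numeric score.

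**The size of the loss can be overstated.** A reader might infer that more than half the power is lost. At r = 0.5 that holds for Fisher up to about d = 1.0. It does not hold for chi-square, which is named first and would be the usual choice with a central cut.

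**Phase II would not be left empty-handed.** A reader might infer that no effect size or SD would be available. The promise of descriptive statistics for all analysed parameters contradicts that, since means and SDs by arm are ordinary descriptive statistics. What they would lack is the baseline-adjusted difference and its confidence interval.

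**Power is a weak yardstick here, and model detail belongs in a fuller document.** The first half stands: this is an exploratory pilot with no power target, and at d = 0.5 even ANCOVA reaches only 33%. The second half does not remove the point. The article does not leave the method open; it names one that suits only part of the primary endpoint. A fuller plan may well name another for the scores, but that would depart from the published statement.

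**Conclusion.** The point holds in a limited form. The one between-arm method stated suits counts, while OABSS and IPSS are numeric, belong to the primary acute-toxicity endpoint and have a pre-radiotherapy value. If they were cut at the midpoint and baseline left out, the relative loss against ANCOVA would be about 25–46% with chi-square and 42–72% with Fisher. That range rests on the assumed level, normality, correlation of 0.5 and differences of 0.5–1.2 SD; a different cut or correlation moves it, as shown in the working. The consequence is less precise patient-reported information for designing phase II, not a failed confirmatory test. It is worth correcting because the better analysis uses data already planned for collection.

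**What to change.** Amend the Statistical analysis section as follows:

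- Keep chi-square/Fisher for binary CTCAE endpoints.
- Compare OABSS and IPSS totals by allocated dose with ANCOVA, or with a repeated-measures model over the visits inside the acute window (end of boost and 1 month).
- Adjust for the pre-radiotherapy score. Use the end-of-WPRT score instead only if it is recorded before the allocation is known: 20 weekday fractions end at about the fourth week, when blinding ends.
- Report the adjusted difference with its 95% CI, and the SD, for phase II planning.
- Analyse the 4-month scores separately, because that visit lies outside the 3-month acute window.

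The cost is small: revised wording, slightly more analysis work, and a linear-model assumption for bounded scores. No additional visit or measurement is needed.

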## Discussion

A large comprehensive review involving over 52,000 patients reported that combination therapy including EBRT and brachytherapy appears superior to localized treatment alone in intermediate- and high-risk prostate cancer patients [6]. Additionally, Spratt et al. reported that compared with high-dose IMRT alone, brachytherapy in combination with IMRT was associated with better 7-year BCRFS rates (81.4% vs 92.0%, *P* < .001) and better distant metastasis-free survival (93.0 vs 97.2%, *P* = .04) for patients with intermediate-risk prostate cancer [4]. The BCRFS curve was gradually decreased until 10 years after IMRT alone, whereas there was no BCR incidence after approximately 7 years after the combination therapy. A recent Canadian phase III study demonstrated that patients receiving low-dose-rate brachytherapy boost were twice as likely to be free of BCR compared with those receiving dose-escalated EBRT boost [5]. They also reported that 5-, 7-, and 9-year BCRFS rates were 89%, 86%, and 83% with brachytherapy boost and 84%, 75%, and 62% with EBRT boost, respectively (*P* < .001). Similar to Spratt et al., the BCRFS curves for the treatment arms in the Canadian study sharply diverged after 4 years, and PSA control with brachytherapy boost reached a plateau after approximately 8 years compared with the continuous BCR events in the EBRT boost arm. Therefore, the advantage of combination therapy should increase with longer follow-up.

Despite better PSA control, one disadvantage of brachytherapy is the invasive procedure that requires anesthesia, pain control, and hospitalization. A dosimetric study found that CyberKnife could achieve the dose distribution of brachytherapy [7]. The difference of PTV receiving 100% of prescribed dose between CyberKnife and brachytherapy plans was measured only 0.5% (96.5% with CyberKnife vs 96.0% with brachytherapy). Furthermore, CyberKnife plans showed lower urethra doses and a rapid rectal dose fall off, suggesting a potential reduction in toxicities. More importantly, CyberKnife is non-invasive and controls intra-fractional movement through real-time fiducial tracking. Through the introduction of SBRT to boost therapy, overall treatment time can also be shortened to 5 weeks. SBRT itself has the potential to increase the therapeutic ratio as well, given that prostate cancer was reported to have a low α/β ratio with high sensitivity for large fraction sizes [8].

This trial uses PRO as well as CTCAE toxicity criteria for accurate assessment of toxicities. Although the CTCAE criteria are the “gold standard” for evaluating adverse events, attempts to capture patient perspective via PRO are increasing. A previous study found that agreement between the CTCAE criteria and PRO was poor to moderate [20]. Another study found that the number of patients reporting severe neuropathy (30%) was higher than that identified by the CTCAE criteria (10%), which suggested that toxicities were often undetected or underestimated by clinicians [21]. As a pilot trial, toxicity assessment is an essential endpoint, and this trial is anticipated to evaluate complications more precisely using PRO.

The goal of this prospective, single-center, pilot trial is to evaluate acute toxicities and short-term biochemical control after ADT and WPRT followed by SBRT boost. We attempt two boost dose schemes (18 Gy/3 fractions vs 21 Gy/3 fractions). We anticipate acceptable acute toxicities and favorable short-term control of PSA in intermediate- and high-risk prostate cancer patients who receive the combination treatment of ADT, WPRT, and SBRT boost. We will design the full-scale phase II study for selecting the boost dose referring to the data from the present pilot study.

## Trial status

Patient recruitment has not yet been completed.

## Abbreviations

ADT: Androgen-deprivation therapy
BCR: Biochemical recurrence
BCRFS: Biochemical recurrence-free survival
BED: Biological effective dose
CT: Computed tomography
CTCAE: Common Toxicity Criteria for Adverse Events
CTV: Clinical target volume
EBRT: External-beam radiotherapy
GTV: Gross target volume
IMRT: Intensity-modulated radiotherapy
MRI: Magnetic resonance imaging
OAR: Organs-at-risk
PRO: Patient-reported outcomes
PSA: Prostate-specific antigen
PTV: Planning target volume
SBRT: Stereotactic body-radiotherapy
WPRT: Whole-pelvic radiotherapy
